## Abstract

**Background:**

Obesity rates in adults continue to rise and effective treatment programs with a broad reach are urgently required. This paper describes the study protocol for a web-based randomized controlled trial (RCT) of a commercially available program for overweight and obese adult males and females. The aim of this RCT was to determine and compare the efficacy of two web-based interventions for weight loss and maintenance of lost weight.

**Methods/Design:**

Overweight and obese adult males and females were stratified by gender and BMI and randomly assigned to one of three groups for 12-weeks: waitlist control, or basic or enhanced online weight-loss. Control participants were re-randomized to the two weight loss groups at the end of the 12-week period. The basic and enhanced group participants had an option to continue or repeat the 12-week program. If the weight loss goal was achieved at the end of 12, otherwise on completion of 24 weeks of weight loss, participants were re-randomized to one of two online maintenance programs (maintenance basic or maintenance enhanced), until 18 months from commencing the weight loss program. Assessments took place at baseline, three, six, and 18 months after commencing the initial weight loss intervention with control participants repeating the initial assessment after three month of waiting. The primary outcome is body mass index (BMI). Other outcomes include weight, waist circumference, blood pressure, plasma markers of cardiovascular disease risk, dietary intake, eating behaviours, physical activity and quality of life.

Both the weight loss and maintenance of lost weight programs were based on social cognitive theory with participants advised to set goals, self-monitor weight, dietary intake and physical activity levels. The enhanced weight loss and maintenance programs provided additional personalized, system-generated feedback on progress and use of the program. Details of the methodological aspects of recruitment, inclusion criteria, randomization, intervention programs, assessments and statistical analyses are described.

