## Study aim

The aim of this paper is to report the study protocol used in an RCT examining the efficacy of a commercially available online weight loss program on initial weight loss and maintenance of lost weight up to 18 months.

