#### Phase 1 - Weight-loss interventions

Participants were initially randomized to one of three groups:

(1) Group 1, wait-list control; subsequently re-randomized to Group 2 or 3 after an initial 12-week control period;

(2) Group 2 followed the standard (Basic) commercial online weight loss program;

(3) Group 3 followed an extra support (Enhanced) version of the online weight loss program and received system-generated personalized feedback, based on diary entries and website use.

At the end of the initial 12 weeks of weight loss, those in Groups 2 and 3 could choose to undertake a further 12 weeks of weight loss or if they had achieved their goal weight, which was a loss of a minimum of 10% of initial body weight, they were re-randomized to one of two maintenance of lost weight programs (Phase 2).

#### Phase 2

Maintenance Group 1 (M1) was usual care whereas Maintenance Group 2 (M2) was enhanced support. Phase 2 will run for 12 months for those commencing after 6 months of weight loss or for 15 months for those entering after only 12 weeks of weight loss.

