### Phase 1 - Weight-loss interventions

The interventions are delivered online for 12 weeks, with new program content distributed to the user weekly for both programs. At the end of 12 weeks participants could choose to repeat the same 12-week weight-loss program, or continue for an additional 12 weeks with the accumulated program content all available, or transfer to weight-loss maintenance if they lost a minimum of 10% of their baseline weight.

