#### Group M1 Basic maintenance of lost weight program

• Continued access to the online program for a further 12 months, including online forum access.

• Adjusted daily Calorie target for weight maintenance.

• Weekly menu plans and exercise programs according to individual preferences, adjusted for the user's maintenance Calorie target.

• Continuation of weekly educational tips and challenges based upon food, activity and lifestyle, including four consecutive weeks of maintenance-specific content.

• A certificate to celebrate the achievement of goal weight or reaching the maintenance phase.

• Weekly email and phone text prompts to continue entering body weight and other body measurements.

• Maintenance-specific feedback on weigh-ins including warnings if the user's weight is creeping up.

• Access to an online information page detailing evidence-based behavioural strategies to enhance the likelihood of weight loss maintenance (e.g., eat breakfast; continue to monitor diet and physical activity; follow a low fat, low energy dense eating plan; be active for one hour a day; limit take-away and fast food; moderate week-end eating; react quickly when weight gain is observed).

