### Data analysis

Analysis will be on an intention-to-treat basis. Analysis of covariance will be used to test for differences in weight loss between groups at 3 months. The model will be fitted using linear regression with weight at 3 months as the outcome variable, treatment group as the predictor variable of interest and weight at baseline included as a covariate. Other independent variables included in the model will be: gender, kilojoule intake at baseline and physical activity at baseline. Differences in weight loss between groups in the weight maintenance phase will be analysed using generalised linear mixed models (GLMM). The outcome in the model will be the individual's weight at the post treatment assessments, the main predictor of interest will be treatment group and baseline weight will be included as a covariate. Other independent variables included in the model will be: time, gender, kilojoule intake at baseline and physical activity at baseline.

Statistical significance of the primary efficacy analysis (at three months and 18 months) will be based on Hochberg's multiple testing procedure with the family wise error rate for each time point held at 2.5%. All secondary hypothesis tests will be performed using a 2-sided 5% significance level. In addition, linear regression and GLMM will be used to describe relationships among the various dependent and independent variables.

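### Phase 2 entry at 24 weeks has no stated minimum loss and the Phase 2 model ignores loss at re-randomization, so the 18-month M1-M2 contrast is not specific to maintenance of lost weight

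*Protocol article*

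**What the plan says.** - **Aim.** The abstract's Background gives the aim as "to determine and compare the efficacy of two web-based interventions for weight loss and maintenance of lost weight". The Study aim section speaks of the "efficacy of a commercially available online weight loss program on initial weight loss and maintenance of lost weight up to 18 months".
- **Entry at 12 weeks.** The design section on Phase 1 says that "if they had achieved their goal weight, which was a loss of a minimum of 10% of initial body weight, they were re-randomized". The later Phase 1 section on the interventions repeats the condition: participants could "transfer to weight-loss maintenance if they lost a minimum of 10% of their baseline weight".
- **Entry at 24 weeks.** The abstract's Methods/Design says that "otherwise on completion of 24 weeks of weight loss, participants were re-randomized to one of two online maintenance programs". No minimum loss is attached. The section Phase 2 - Maintenance of lost weight says only that the phase begins when the weight loss phase ends.
- **Entry below goal is foreseen.** The M1 programme includes "A certificate to celebrate the achievement of goal weight or reaching the maintenance phase".
- **Analysis.** The Data analysis section says "Differences in weight loss between groups in the weight maintenance phase will be analysed using generalised linear mixed models (GLMM"). The outcome is weight at the post-treatment assessments. Treatment group is the predictor of interest. The covariates are baseline weight, time, gender, baseline kilojoule intake and baseline physical activity. Eighteen months is one of the two primary time points.
- **Randomization.** Re-randomization is done in the same way as the first allocation, which was stratified by gender and BMI category. Loss in Phase 1 is not named as a stratum.

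**The concern.** Maintenance of lost weight is defined only for someone who has lost weight. If Phase 2 includes people who have not, the all-entrant contrast estimates the effect of M2 against M1 on later weight in a mixed population, and the model has no term that shows where an effect arises.

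This affects how the 18-month result is read. A null result could mean that M2 does not prevent regain, or that many entrants had little to regain. A difference in favour of M2 could reflect better retention of lost weight, or different weight change in people who had lost little. The stated model cannot distinguish these, yet the phase's name invites a conclusion about maintenance. The article sets out the model, outcome and covariates for a primary time point, so the point concerns what is stated and not a detail left to a later document.

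**Working it through.** **1. The plan's own figure.** Inputs from Sample size: difference 1.5 kg/m², SD 1.5 kg/m², two-sided alpha 0.05, power 90%.

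n per arm = 2(z₀.₉₇₅ + z₀.₉₀)² × (1.5/1.5)² = 2(1.960 + 1.282)² ≈ 21.0, so 22 per arm; 23 by the noncentral t. The stated 48 per maintenance group is 24 per sex, so it fits if the calculation was made within each sex. No allowance for entrants without a loss appears in it.

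**2. What the model measures under each reading of baseline weight.** Compare a participant who lost 12% in Phase 1 and held it with one who lost nothing and stayed there.

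| Baseline weight means | What the model estimates | The two participants |
|---|---|---|
| Weight at programme start | Total change to 18 months; Phase 1 loss and later change are mixed | 12% apart |
| Weight at Phase 2 entry | Change since re-randomization, averaged over people with and without a loss | Both unchanged |

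The second reading is closer to a regain contrast, but it treats holding a loss and never having had one alike. Neither reading is specific to maintenance.

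**3. How many entrants might have little to maintain.** The article gives no expected 24-week loss, so everything here is assumption. Take BMI loss as normal with SD 1.5 (borrowed from Sample size, where it is called the SD of BMI) and entry BMI 32, so that 5% and 10% are 1.6 and 3.2 kg/m². With Φ the standard normal distribution function and m the mean loss:

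- no loss: Φ(−m/1.5)
- under 5%: Φ((1.6 − m)/1.5)
- 10% or more: 1 − Φ((3.2 − m)/1.5)

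| m (kg/m²) | No loss | Under 5% | 10% or more |
|---|---|---|---|
| 1.5 | 16% | 53% | 13% |
| 2.0 | 9% | 40% | 21% |
| 3.0 | 2% | 18% | 45% |

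A second set of assumptions (mean loss 3% to 7% of weight, SD 4% to 6%) gives 4% to 31% with no loss, 16% to 50% under 3%, and 69% to 96% under 10%. If the programme's target of 0.5 to 1 kg per week were met throughout, the loss over 24 weeks would be 12 to 24 kg and the share with no loss negligible.

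**4. What dilution would do.** Suppose a share s gets no M2 effect and the rest get effect d. The pooled effect is d(1 − s). Two-sample t power with 48 per arm, SD 1.5 and two-sided alpha 0.025 (the family-wise level per time point in Data analysis):

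| d (kg/m²) | s = 0 | s = 0.16 | s = 0.53 |
|---|---|---|---|
| 1.5 (the plan's difference) | effect 1.50, power 99.5% | 1.26, 97% | 0.71, 51% |
| 1.0 (illustration) | effect 1.00, power 84% | 0.84, 68% | 0.47, 23% |

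The s = 0.53 column counts everyone below 5% loss as having nothing to maintain and no M2 effect. That is an extreme assumption: a person who lost 4% can regain it.

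**The case against.** The strongest reply is that offering a maintenance programme to everyone who completes 24 weeks is a coherent pragmatic design. The contrast is randomized, the primary outcome is BMI, and the article promises neither a regain outcome nor a population with a minimum loss. Subsets and interactions are commonly left to an analysis plan, and the article foresees further regression work. Much of this stands. The missing subset is not in itself a fault. What remains is that the model stated for a primary time point, with an undefined baseline, does not match the aim as worded.

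A reader might infer several stronger things that the documents do not support:

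- **That a sizeable share of entrants had nothing to maintain.** No figure is given. Below-goal entry is likely to be common under the assumptions above, but the share with no loss ranges from negligible to about 31%. The certificate wording shows entry below the 10% goal; it does not show entry after any weight change. That rests on the absence of a stated minimum.
- **That the M1-M2 comparison is biased.** It is not: allocation is random among all entrants.
- **That maintenance and other weight change cannot be separated.** Weight is measured at 3 and 6 months, so loss at entry is known. Only the model as written leaves it out.
- **That the trial is underpowered for this reason.** At the plan's own 1.5 kg/m², 16% dilution leaves power at about 97%. The low figures need a smaller effect or the extreme threshold.
- **That a benefit could easily be late first-time loss.** M1 sets its Calorie target for maintenance and M2 contains all of M1. The only weight loss programme named in Phase 2 is the M2 relapse component, triggered by a rebound. This route is possible but not prominent.

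**Conclusion.** The point holds as a mismatch between the stated question and the analysed population and model. Entry at 12 weeks requires a 10% loss, entry at 24 weeks has no stated minimum, and the Phase 2 model takes no account of loss at re-randomization. The M1-M2 contrast is valid for the effect on 18-month weight or BMI among everyone entering Phase 2, but is not specific to maintenance of lost weight.

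Its size is unknown. That most entrants miss 10% is fairly robust across the assumptions tried (55% to 96%), unless the programme's weekly target is met in full. A large share with no loss at all is not robust. Any loss of power depends on the assumed effect and on assuming no M2 effect in people without a loss. The point should be acted on because it affects how a primary result is described and costs little to settle.

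**What to change.** Leave entry and treatment as they are, and change the Data analysis section:

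1. Keep the all-randomized M1-M2 contrast as primary, and describe it as the effect on 18-month BMI or weight among all Phase 2 entrants.
2. Define baseline weight in the Phase 2 model, and include percent loss (or weight) measured at re-randomization as a covariate.
3. Pre-specify as supportive analyses a treatment-by-percent-loss interaction in the full set, and the M1-M2 contrast with numbers per arm among those above a fixed loss threshold, for example 5% of starting weight. Read any statement about maintenance of lost weight together with these. Because percent loss is measured before M1/M2 allocation, the subset comparison is still randomized.

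Separately, the sponsor should reconcile the two entry rules with the stated aim.

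**Cost.** Wording, one covariate and two supportive models on weights already scheduled; no new visits or participants. The price is precision. The standard error of the contrast is 1.5 × √(2/n): 0.31 kg/m² with 48 per arm, 0.34 with 40 (84% of 48) and 0.44 with 23 (47% of 48). The interaction will also be imprecise. A 10% threshold could leave about 6 per arm (13% of 48) under the lowest assumed loss, with power of 11% for an effect of 1.0 and 24% for 1.5, so the threshold should be chosen with this in mind and the subset kept supportive.

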**Discussion:**

Importantly, this paper describes how an RCT of a currently available commercial online program in Australia addresses some of the short falls in the current literature pertaining to the efficacy of web-based weight loss programs.

Australian New Zealand Clinical Trials Registry (ANZCTR) number: ACTRN12610000197033

## Background

Obesity is a major health problem in Australia [1], just as it is internationally, and is associated with a range of adverse physiological and psychological consequences [2]. By 2000, 67% of men and 52% of women [3] in Australia over 24 years of age were measured objectively as being overweight (Body Mass Index (BMI) >25) or obese (BMI >30). The 5-year AusDiab follow-up study demonstrated that 200,000 adults progress from being overweight to obese each year [2]. Consequently, developing strategies to target obesity treatment and prevention is a national priority.

In 2008, the total financial cost of obesity in Australia was estimated to be $8.28 billion. This increases to $58.2 billion if indirect costs such as loss of wellbeing are included [4]. Although prevention of excess weight gain is the ultimate solution, even moderately effective treatments have the potential to improve health and curb heath care costs. For example, the Diabetes Prevention Program has shown that a 57% reduction in the risk of developing type-2 diabetes can be achieved by a weight loss of 5% of initial weight, if maintained for two years [5].

The proportion of the population desiring to lose weight, for either health or aesthetic reasons, is increasing [6] and has contributed to the growth of commercial weight programs, such as Weight Watchers and Jenny Craig and relatively new internet-based weight loss programs such as The Biggest Loser Club. However, industry-delivered weight loss programs, including those that are web-based, are rarely evaluated using rigorous research designs [7]. Further, health professionals may be hesitant to recommend commercial weight loss programs unless they are evidence-based and/or they have been shown to be efficacious.

Accessing health services for obesity treatment is limited with inequitable services relative to population distribution. Internet-based weight loss programs have the potential to provide a service to large numbers of people, be widely accessible (metropolitan, regional, rural, remote, international) and cost effective for the individual. Web-based weight management is under-explored relative to the rapid uptake of the Internet by adults in Australian home environments. Currently in Australia 72% of households have access to the Internet and although there are lower access rates in rural and remote areas and among households with lower weekly incomes [8], we have previously shown that a web-based weight loss program is of interest to those in 'hard-to-reach' groups such as males, younger people, living in rural and remote locations [9]. Internet programs may overcome traditional barriers to weight loss treatment due to 24 hour a day accessibility, affordability and anonymity for those who may avoid seeking treatment due to embarrassment or other reasons [10]. It can also provide a forum for social support through e-mail, bulletin boards, chat rooms, group forums and web-hosted meetings [11]. Importantly, it can minimize participant burden and irritation associated with group sessions or clinic visits [12], particularly time spent in waiting rooms, and has the potential to be used in a broad range of settings to optimise weight outcomes for patients.

## The evidence base for web-based weight loss

We recently published a systematic review and meta-analyses examining the efficacy of Internet-based weight loss programs [13]. Of the 18 studies identified, seven were assessed for effectiveness based on percentage weight change and four were deemed effective. However, it was not possible to clearly establish the efficacy or the effectiveness of web-based interventions on weight loss due to the heterogeneity of study designs. Whether Internet-based programs are effective at achieving weight loss that is subsequently maintained is also largely undetermined [13]. Although greater use of website features may increase weight loss, we do not know which specific components are more important or can reduce attrition. Therefore, examining the efficacy of commercially available Internet delivered weight management interventions, and determining the specific contributions of self-monitoring of diet, physical activity and body measurements, as well as use of features such as online support, are warranted.

## Study aim

The aim of this paper is to report the study protocol used in an RCT examining the efficacy of a commercially available online weight loss program on initial weight loss and maintenance of lost weight up to 18 months.

## Design and methods

### Ethics approval

The University of Newcastle's Human Ethics Research Committee approved this study. Written informed consent was obtained from all participants prior to their enrolment.

### Design - Randomized Control Trial

A prospective randomized controlled trial conducted in adult participants that were classified as overweight or obese. The study consisted of two phases: a weight loss phase (Phase 1) followed by a maintenance of lost weight phase (Phase 2).

#### Phase 1 - Weight-loss interventions

Participants were initially randomized to one of three groups:

(1) Group 1, wait-list control; subsequently re-randomized to Group 2 or 3 after an initial 12-week control period;

(2) Group 2 followed the standard (Basic) commercial online weight loss program;

(3) Group 3 followed an extra support (Enhanced) version of the online weight loss program and received system-generated personalized feedback, based on diary entries and website use.

At the end of the initial 12 weeks of weight loss, those in Groups 2 and 3 could choose to undertake a further 12 weeks of weight loss or if they had achieved their goal weight, which was a loss of a minimum of 10% of initial body weight, they were re-randomized to one of two maintenance of lost weight programs (Phase 2).

#### Phase 2

Maintenance Group 1 (M1) was usual care whereas Maintenance Group 2 (M2) was enhanced support. Phase 2 will run for 12 months for those commencing after 6 months of weight loss or for 15 months for those entering after only 12 weeks of weight loss.

### Outcome measures

Assessments were at baseline, 3, 6 and 18 months. The Phase 1, Group 1 control participants received an extra assessment at the end of the initial waiting list control period and were then also evaluated at 3, 6 and 18 months from the start of weight loss, meaning they will participate for a total of 21 months.

### Participants and recruitment

Participants were recruited in the Hunter region of NSW, Australia through advertising (radio, TV, newspapers, flyers in GP clinics, University website, workplace-based emails) and using the University media unit. Inclusion and exclusion criteria are summarised in Table 1.

**Table 1 T1:** Inclusion and exclusion criteria for recruitment into the Biggest Loser Club RCT.

Inclusion Criteria	Exclusion Criteria
Aged between 18 and 60 years	Currently pregnant or trying to become pregnant
BMI between 25 and 40 kg/m^2^	History of major medical problems such as heart disease or diabetes requiring insulin treatment
Agree to not participate in other weight loss programs during the study	Orthopaedic or joint problems that are a barrier to physical activity
Pass a health-screening questionnaire and available for assessment sessions [23]	Recent weight loss of ≥ 4.5 kg in previous 6 months
Have access to a computer with e-mail and Internet facilities	Taking medications that might be affected by weight loss or affect weight loss

